## Abstract

**Background:**

The current food pyramid guidelines have been criticized because of their complexity and the knowledge required for users to understand the recommendations. Simplification of a dietary message to focus on a single key aspect of dietary quality, e.g., fiber intake, may make the message much easier to comprehend and adhere, such that respondents can achieve greater weight loss, better dietary quality and overall metabolic health.

**Methods and design:**

This is a randomized controlled clinical trial with two equal sized arms. In total, 240 obese adults who meet diagnostic criteria for the metabolic syndrome will be randomized to one of the two conditions: 1) a high fiber diet and 2) the American Heart Association (AHA) diet. In the high fiber diet condition, patients will be given instruction only on achieving daily dietary fiber intake of 30 g or more. In the AHA diet condition, patients will be instructed to make the several dietary changes recommended by the AHA 2006 guidelines. The trial examines participant weight loss and dietary quality as well as changes in components of the metabolic syndrome, inflammatory biomarkers, low-density lipoprotein cholesterol levels, insulin levels, and glycosolated hemoglobin. Potential mediators, i.e., diet adherence and perceived ease of the diet, and the intervention effect on weight change will also be examined.

**Discussions:**

The purpose of this paper is to outline the study design and methods for testing the simple message of increasing dietary fiber. If the simple dietary approach is found efficacious for weight loss; and, improves dietary quality, metabolic health, and adherence, it might then be used to develop a simple public health message.

**Trial registration:**

NCT00911885

## Background

Metabolic syndrome affected nearly 27% of US adults in 2006, and due to rising obesity rates, the prevalence of metabolic syndrome is likely much higher in 2009. Metabolic syndrome is strongly associated with poor dietary quality [1], and treating it is one of the keys to the prevention of cardiovascular disease (CVD) [2,3] and diabetes [4,5]. Research is needed on interventions that effectively treat metabolic syndrome, preventing its advance to the physical, mental, and financial costs of CVD and diabetes.

The impact of public health campaigns is maximized when a health message is simple and easy to understand [6]. Dietary guidelines like those put forth by the American Heart Association (AHA), US Department of Agriculture (USDA), and the American Diabetes Association (ADA) [7-9] are based on research and are in the interest of public health but are also complex involving multiple macronutrients, each with differing recommended portion sizes and daily servings. A healthy diet is key to CVD and diabetes prevention but we are lacking a simple, effective public health message to improve the American diet.

A simple dietary message is only possible to the extent that one area of diet is identified that, on the one hand, has a strong impact on overall dietary quality and disease prevention, and on the other hand, is associated with good adherence and acceptability. One possible area of diet that could meet these two criteria is dietary fiber. Dietary fiber has been demonstrated to be a useful component of weight loss and weight loss maintenance [10-12] and it acts directly on several aspects of the metabolic syndrome including decreasing waist circumference and body weight, glucose and lipid homeostasis, and improving hypertension and insulin control [13,14].

### Body weight and waist circumference

Observational and review studies have indicated an inverse relationship between dietary fiber intake, body weight and waist-to-hip ratio ([10-12] with several relatively short-term intervention studies further supporting the relationship between a high fiber diet and moderate reductions of body weight and waist circumference [15-17]. Epidemiologic studies support a strong negative association between dietary fiber intake and obesity. However, a limited number of clinical trials have been conducted directly associating a simple dietary fiber message with metabolic components, including the mechanism by which fiber acts. Howard and colleagues concluded from 12 published intervention studies that under conditions of fixed energy intake, an increase in dietary fiber intake increased post-meal satiety and decreased subsequent hunger [10]. When energy intake is ad libitum, increasing consumption of dietary fiber is associated with weight loss via a decrease in energy intake. A review by Lairon also supports these results [12]. It is proposed that high-fiber foods promote satiety through delayed gastric emptying, increased food volume, and increased chewing, which attenuates the return of hunger [18,19], and leads to decreased energy intake. In fact, Pereira and colleagues reviewed 27 clinical studies and concluded that most studies showed that an increased fiber intake correlates with a reduced energy intake of 10% [18]. In addition, fiber decreases the absorption efficiency of the small intestine ([11].

### Insulin resistance and hypertension

An increased intake of total fiber is inversely associated with markers of insulin resistance and reduced diabetes risk [20-22]. The Insulin Resistance Atherosclerosis Study showed that dietary fiber was significantly associated with insulin sensitivity, fasting insulin, body mass index (BMI), and waist circumference [22]. Similarly, in the Inter99 study, intake of dietary fiber was inversely associated insulin resistance estimated using the homeostasis model assessment of insulin resistance (HOMA-IR) [21]. In addition, soluble dietary fiber has been reported to reduce postprandial glucose levels and to improve insulin sensitivity [23,24]. These findings support the recommendation to increase intake of fiber-rich carbohydrates to prevent insulin resistance [25]. Clinical trials indicate that a diet high in fiber decreases blood pressure in hypertensive and obese individuals [26,27]. Since insulin resistance with compensatory hyperinsulinemia has been named a major pathogenic vehicle for the development of hypertension [28], reducing insulin resistance through increasing dietary fiber intake may help treat or prevent hypertension. In addition, increasing dietary fiber intake promotes weight loss and deters weight gain, both of which would likely have a large impact on the prevention and burden of hypertension.

### Inflammation biomarkers

Observational studies draw a significant link between dietary fiber intake and reduced levels of C-reactive protein (CRP) [29-32]. In a small clinical trial of 28 subjects, King and colleagues demonstrated that increasing fiber lowered the levels of CRP [33]. We have discussed four possible mechanisms between dietary fiber and inflammation in our two recent publications [31,32]. First, dietary fiber decreases lipid oxidation, which in turn is associated with decreased inflammation [34]. Second, dietary fiber supports normal bowel flora as part of an optimal intestinal environment, which helps to prevent inflammation [34]. Third, dietary fiber may inhibit inflammation through its beneficial effects on glycemic control [35,36]. Finally, diets high in fiber may increase plasma adiponectin concentrations in diabetic patients: adiponectin has been found to have profound anti-inflammatory effects [37].

### Glycemic and lipid control

In a crossover design of 11 patients with metabolic syndrome, patients supplemented a high-carbohydrate diet with soluble fiber for 3 weeks [38]. Results indicate that a high fiber diet improves glycemic control, total and LDL cholesterol, while triglycerides and HDL cholesterol remained unchanged.

Our preliminary pilot study data suggest that simply focusing on increasing dietary fiber is equivalent or better than a low-saturated fat message at inducing clinically significant improvement of dietary quality, and may be superior for long-term adherence [39]. Participants were randomized to receive either a simple message to increase fiber intake, a simple message to reduce saturated fat intake, or a combination to increase fiber and reduce saturated fat. At 3 months, participants in the fiber arm increased their fiber intake by 44% and vicariously reduced their saturated fat intake by 25%. Participants in the saturated fat arm reduced their saturated fat intake by 25% but their fiber intake only changed by 2%. These changes were maintained at 6 months. The dual message arm did not show any significant improvement over the dietary fiber arm alone. Patients in the high fiber group lost 7 lbs at 3 months, and 10 lbs at 6 months. The single message of increasing dietary fiber might be more acceptable by encouraging *increases *in intake of particular foods as opposed to depriving messages about eliminating foods. When asked at 3 months about confidence in adhering to the study diet, 85% of participants in the high fiber group felt very or extremely confident they could adhere to the recommendation, while only 50% of participants in the decrease saturated fat condition and 40% of participants in the combination condition felt this way.

We hypothesize that a simplified dietary recommendation focusing on a single aspect of dietary quality - fiber intake - will facilitate weight loss, and improve both metabolic health and overall dietary quality. Such a simplified dietary advisory is easier to follow, and may have beneficial collateral effects on other areas of diet (e.g., reduced caloric and saturated fat intake, and increased intake of protective foods). Such a simple message, if found efficacious for weight loss, metabolic health and dietary quality in a clinical setting, might then be an ideal message for public health settings.

### Research Goals

The overall goal of the present study is to compare the efficacy of two dietary intervention approaches on weight loss and improving dietary quality among patients with the metabolic syndrome. One approach is complex and the other is simple. The two approaches are: 1) the AHA Dietary Guidelines [40] that is currently recommended to patients with the metabolic syndrome [41,42]; and 2) a high fiber diet that provides instruction on a single area of diet, fiber. Secondary research goals include examining changes in components of the metabolic syndrome, inflammatory markers, low-density lipoprotein (LDL-C) cholesterol levels, insulin levels, and glycosolated hemoglobin (HbA1c). We hypothesize that the high fiber condition will significantly improve overall diet quality and metabolic health over the AHA condition. Additionally, potential mediators (i.e., adherence and perceived ease of the diet) of the intervention effect at 12 months will also be examined.

## Methods/Design

### Study Design

The study protocol was approved by the University of Massachusetts Medical School's (UMMS) Institutional Review Board. Two hundred forty adults (50% female) who meet diagnostic criteria for the metabolic syndrome will be randomized to the high fiber condition or the AHA diet condition. The study was funded by the National Heart, Lung and Blood Institute.

### Subject Eligibility Criteria

To be eligible for the study, an individual must: 1) Meet diagnostic criteria for the metabolic syndrome [43]; 2) Be interested in losing weight and have a BMI 30-40 kg/m^2^; 3) Be between 21 to 70 years old; 4) Have a telephone in the home or easy access to one; 5) Provide informed consent; 6) Have physician approval to participate in the study; 7) Be a non-smoker (given nicotine's effect on weight suppression, on HDL-C, and smoking cessation's effect weight gain); and, 8) Be able to speak and read English.

An individual will be excluded from participation if he/she:1) Has clinically diagnosed diabetes, or a fasting blood sugar of ≥ 126 mg/dl; 2) Had an acute coronary event within the previous 6 months; 3) Is pregnant or lactating; 4) Is a woman with polycystic ovary syndrome [44]; 5) Plans to move out of the area within the 12-month study period; 6) Has a diagnosis of a medical condition that precludes adherence to study dietary recommendations (e.g., Crohn's disease, ulcerative colitis, active diverticulitis, renal disease); 7) Has elevated depression or suicidal ideation; 8) Is following a low-carbohydrate, high-fat dietary regimen such as the Atkins' Diet [45]; 9) Is participating in any current weight loss program; 10) Has had bariatric surgery or is currently using weight loss medication; or, 11) Has been diagnosed with an eating disorder (bulimia nervosa or binge eating).

### Recruitment

Study recruitment began in May 2009. Recruitment strategies include: posting study recruitment fliers at the University of Massachusetts Medical School (UMMS), local public libraries and churches; announcements on the UMMS intranet; recruitment ads in the local newspapers and on Craigslist; and targeted direct mailings. All IRB approved posters and advertisements include a phone number that individuals can call. Potential subjects responding to study advertisements receive an explanation of the study and are screened via telephone using a brief questionnaire focused on inclusion and exclusion criteria. This information is retained in a database with Lotus Notes/IBM tracking system software (Lotus Notes R5.0.11^®^) developed specifically for this study. When an individual is found to be pre-eligible for the study and expresses interest in participating, a screening appointment is then scheduled.

The University is currently updating its clinical data system and once it is complete, we will be able to identify patients who are eligible using a primary care patient population database. A HIPAA-IRB waiver will be obtained to identify eligible patients.

### Study Measures at Screening Visit, Baseline Visit and Patient Follow-up

At the screening visit, a screening consent form is reviewed and signed. The Cholestech LDX System™ is used to measure HDL-C, triglycerides, and glucose from a fasting fingerstick with results produced within 10 minutes. Individuals are asked to fast 12-hours prior to the appointment. Patients have their height and weight measured in stocking feet via an electronic digital scale (Scale-Tronix, Carol Stream, Illinois, Model 5002 Stand-On Scale). Waist is measured twice at the narrowest part of the torso (or a site between the lower rib and crest of the hipbone). Blood pressure is also measured two times: initially after sitting quietly for 10 min, then again after 2 minutes using a Dinamap XL ^® ^automated BP monitor (Critikon). The Center for Epidemiological Studies-Depression Scale (CES-D)[46,47] is administered to assess for depression. Individuals with CES-D >= 21, indicating severe depressive symptoms [48], are excluded from participation. Medical clearance is then requested from the primary care physician, and individuals found to be eligible are invited back for a baseline visit.

At the baseline visit, a second study consent form is reviewed with the research assistant and signed. A fasting blood sample, anthropometric measures, and medication and supplement information are collected, which will again be assessed at the 3-, 6-, and 12-month visits. A questionnaire packet assessing demographic information and psychosocial variables is completed at baseline, 3-, 6- and 12-month visits. Three 24-hour diet and physical activity recalls are collected within a three-week window at baseline, 6- and 12-month visits to determine individual dietary and physical activity change, and one 24-hour recall is collected at 3 months to determine group differences. The 3-month visit assessment will measure short-term changes in body weight and metabolic syndrome indicators, however, inflammatory markers, insulin, and HbA1c will not be measured. Table 1 includes a complete list of study measures and the timing of these measures. Patients receive a stipend of $10 at baseline and the 3 month assessment; $20 at the 6-month assessment; and $40 at the 12 month assessment.

**Table 1 T1:** Measurement Schedule

	Timepoint			
**Measure**	**Baseline**	**3 mos**	**6 mos**	**12 mos**

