### Randomization

After providing informed consent and completing the baseline assessment, participants are randomized to one of the two diet conditions. Participants are stratified by gender, age (in deciles), and BMI categories (30-34.9, and >= 35-40 kg/m^2^). Within each strata, participants are randomized to the two conditions in randomly permuted blocks of size 3 and 6 using the ralloc program in Stata [49] to ensure that the distributions of gender, age, and BMI are similar between two conditions. The randomization is carried out by the project director who does not interact with participants.

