### Statistical Analytic Approach for Primary Aim

The high fiber condition is hypothesized to induce greater weight loss than the AHA condition. We will evaluate the intervention effects on change in body weight using general and generalized linear latent and mixed models (GLLAMM) that have been implemented in Stata SE 10 [54,55]. The commonly used linear mixed models are a subgroup of GLLAMM. In the analysis, each patient is assumed to be independent. First, we will carefully evaluate the covariance structure of the outcome variables across time points, and test whether intervention may induce changes in variability in the outcomes. Proper covariance structure will be identified and prescribed in the final analysis. The participant identifier will be included as random effect, time and group as fixed effect. Treatment effect will be tested using time*group interactions in the models.

The analysis will adjust for potential confounders for weight change, including age, gender, baseline BMI, marital status, education attainment, physician advice regarding weight loss and other nutritional advice exposure prior to and during the trial. We also will evaluate the possible interactions between the intervention indicator and these patient's attributes to assess the presence of differential intervention effects among these subgroups. Session attendance will also be included in the models to determine whether this is a dose-response relationship between number of session attended and the extent of weight loss. Statistical approaches to secondary outcomes are very similar, and thus not discussed in detail.

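### Metabolic syndrome components are measured twice before randomization, but the stated secondary approach draws on the baseline value only; adjusting follow-up for both values would gain precision

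*Protocol article*

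**What the plan says.** The protocol article's section on measures at the screening, baseline and follow-up visits describes two measurement occasions before treatment.

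- **Screening, blood analytes:** a fingerstick device "is used to measure HDL-C, triglycerides, and glucose from a fasting fingerstick with results produced within 10 minutes".
- **Screening, waist:** "Waist is measured twice at the narrowest part of the torso".
- **Screening, blood pressure:** "Blood pressure is also measured two times: initially after sitting quietly for 10 min", with a second reading shortly after.
- **Baseline, a separate later visit:** "A fasting blood sample, anthropometric measures, and medication and supplement information are collected, which will again be assessed at the 3-, 6-, and 12-month visits". Table 1 confirms glucose, blood pressure, serum lipids and waist at baseline, 3, 6 and 12 months. It has no screening column.
- **Order:** under Randomization, "After providing informed consent and completing the baseline assessment, participants are randomized to one of the two diet conditions". Both occasions therefore precede allocation.

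Research Goals makes these components secondary outcomes: "Secondary research goals include examining changes in components of the metabolic syndrome, inflammatory markers". The section on the primary aim describes a mixed model with a participant random effect, tests treatment through time*group interactions, and gives an open list of adjustment variables for weight change. No screening value is named. For the rest it says: "Statistical approaches to secondary outcomes are very similar, and thus not discussed in detail".

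**The concern.** A time*group test over a series that begins at baseline compares the arms on change from one baseline value. With complete data and no further adjustment, that is the difference in mean change. Two sources of precision are then unused: regression of follow-up on baseline, and the second pre-randomization value from screening. Both are unaffected by allocation, so adjusting for them cannot bias the arm comparison, even though patients were selected partly on the screening value.

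What is at stake is the width of the confidence intervals for the five components. The sample size was set for body weight alone, so precision on these secondary outcomes is whatever the design happens to deliver.

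**Working it through.** **The plan's own figure.** Sample Size Consideration asks for 95 completers per arm with 20% attrition. 95 / 0.80 = 118.75, so 119, against 120 stated (120 × 0.80 = 96 completers). It reproduces. It concerns weight and does not bear on this point, except that 2 × 95 = 190 completers is used below.

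**Inputs.** The documents give no correlations, so these are assumptions: r01 between screening and baseline, and rf between each of them and a follow-up value. Variances are set to 1.

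**Formulas, one follow-up visit:**
- A, unadjusted change from baseline: 2(1 − rf)
- B, follow-up adjusted for baseline: 1 − rf²
- C, follow-up adjusted for baseline and screening: 1 − 2rf²/(1 + r01)
- D, proportional cut in A from a screening-by-visit term while baseline stays an outcome: (rf − r01)² / [2(1 − rf)]

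Example for r01 = 0.6, rf = 0.5: A = 2 × 0.5 = 1.000; B = 1 − 0.25 = 0.750; C = 1 − 0.5/1.6 = 0.6875. The screening value's share is 1 − 0.6875/0.750 = 8.3%. The whole change is 1 − 0.6875/1.000 = 31%. D = 0.01/1.0 = 1.0%. The equivalent number of completers is 190 × (0.750/0.6875 − 1) = 17.

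| r01, rf | A | B | C | Cut B to C | Cut A to C | D | Extra completers (B to C) |
|---|---|---|---|---|---|---|---|
| 0.60, 0.50 | 1.000 | 0.750 | 0.6875 | 8.3% | 31% | 1.0% | 17 |
| 0.70, 0.55 | 0.900 | 0.6975 | 0.644 | 7.7% | 28% | 2.5% | 16 |
| 0.70, 0.60 | 0.800 | 0.640 | 0.576 | 9.9% | 28% | 1.25% | 21 |
| 0.75, 0.65 | 0.700 | 0.5775 | 0.517 | 10.5% | 26% | 1.4% | 22 |
| 0.60, 0.60 | 0.800 | 0.640 | 0.550 | 14.1% | 31% | 0% | 31 |
| 0.70, 0.70 | 0.600 | 0.510 | 0.424 | 17.0% | 29% | 0% | 39 |

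The first four rows are the main cases. The last two, with all correlations equal, are more favourable. In the main cases baseline adjustment alone (A to B) cuts variance by (1 − rf)/2, that is 25%, 22.5%, 20% and 17.5%, so it supplies most of the 26–31%.

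**Simulation check**, 95 per arm, all correlations 0.7. The mean standard error of the 12-month time*group contrast was 0.1125. It was still 0.1125 with a screening main effect (the estimates agreed to about 4 × 10⁻¹⁵) and 0.1128 with screening by visit. Follow-up adjusted for baseline gave 0.1032, and for baseline and screening 0.0944. The squared ratios are (0.0944/0.1032)² = 0.837, a 16% cut, and (0.0944/0.1125)² = 0.704, a 30% cut. These agree with the table's 17% and 29%.

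**Noisier screening value.** Let baseline correlate 0.7 with follow-up, and screening correlate rs with both. The further cut beyond baseline adjustment is (rs − 0.7rs)² / [(1 − rs²)(1 − 0.49)]:
- rs = 0.6: 0.0324/0.3264 = 9.9%
- rs = 0.5: 0.0225/0.3825 = 5.9%
- rs = 0.4: 0.0144/0.4284 = 3.4%

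**The case against.** The strongest objection is that this is an inference from silence. The covariate list is written for weight change and is open, and the secondary models are expressly not detailed. An article may leave them to a fuller plan, which may already use the screening value. Table 1 schedules measurements and does not say what enters a model. Using baseline as the reference is conventional and valid. All of this stands, and it rules out calling the plan wrong.

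Two stronger readings are tempting.

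- **A reader might infer that one more covariate in the planned model captures the gain.** It does not. While baseline remains an outcome, the screening term gains 1–2.5% in the main cases and nothing when the correlations are equal. The 8–10% needs baseline on the covariate side as well, which changes the model.
- **A reader might infer equal, free precision for all five components.** HDL-C, triglycerides and glucose come from a fingerstick at screening but from a fasting blood sample at baseline, and eligibility restricts the screening range. The documents do not show that the two values are interchangeable. Waist and blood pressure are the cleaner cases.

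The objection does not remove the plain fact that a pre-randomization value will be on file for each component, and that the approach as described makes no stated use of it.

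**Conclusion.** The point holds as an optional improvement to the secondary analyses. It does not identify a bias, a contradiction or an error.

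Under the main assumed correlations, the screening value's own contribution is a variance cut of about 8–10%. That shortens confidence intervals by about 4–5% and is worth roughly 16–22 completers out of 190. For the three blood analytes it may be only 3–10%. The full change of model cuts variance by about 26–31% (intervals 14–17% shorter) against an unadjusted change contrast.

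That larger figure rests on reading time*group as having baseline among the outcomes. If the full plan already adjusts follow-up for baseline, only the screening share remains. Every figure depends on correlations that the documents do not give. Nothing is claimed here for body weight.

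**What to change.** For blood pressure, waist, HDL-C, triglycerides and glucose, state in advance that:

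- the outcomes are the 3-, 6- and 12-month values, with group by visit as the treatment term;
- the baseline value and the screening value enter as two separate covariates, each interacted with visit;
- the two values are not averaged for the fingerstick analytes, because a difference between methods would enter the average;
- change is not measured from screening, because patients were selected partly on that value and it would regress to the mean.

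If the full plan already does this, one sentence in the analysis section would settle the point. The cost is a change in the form of the secondary models and one extra covariate per model. There is no new visit, sample or patient burden.
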